### Process evaluation

To evaluate this complex intervention (aims 3–5), a process evaluation will be used. Process evaluation is a method that can be used when developing, implementing and evaluating complex interventions within a specific context. The method combines quantitative evaluation assessing causal pathways with qualitative methods assessing complex pathways and unexpected mechanisms.^19^ The UK Medical Research Council Guidelines have recognised that process evaluations can assess both the implementation and fidelity of an intervention and identify contextual mechanisms and outcome factors that are specific to the population and context they operate in.^18 19^

The process evaluation in this study will include a quantitative longitudinal prospective evaluation of athlete health outcomes, a cross-sectional and prospective evaluation of health literacy and qualitative evaluation of the development, implementation and effects of the intervention (figure 1). Six months before implementing the web-based platform, all (approximately 150) athletes from the SPKs and the Maties Sports Club, South Africa, will be invited to participate in a longitudinal athlete health surveillance study. Due to a total population design, there is no power calculation. All athletes will be asked to self-report the health outcomes of injuries, illnesses, mental health, sleep, nutrition, time loss from training and training quantity and quality weekly, using the eHealth-based and adapted surveillance system that has been used and evaluated in a previous prospective study.^1^

At the end of 2022, the web platform ‘Safe and Healthy Para sport’ will be implemented online as an open web platform webpage. All athletes will be encouraged to use this web platform each week to improve their overall health knowledge, specifically when experiencing symptoms of an injury, illness or other health concern. The athletes will receive a weekly invitation/reminder about a specific topic to learn more about. Each week’s health topic will also be presented on the project’s social media platforms. The primary outcome is the incidence of injuries and illnesses. Secondary outcomes are the health parameters sleep quantity, nutrition, mental health and the performance indicators training quality and quantity. Data will be analysed by describing incidence rates and proportions. A time-to-event analyses will be conducted. Data will be collected and analysed 6 months before implementation, 6 months after implementation and at 1 year and 4 years following implementation (figure 1).

To evaluate whether the platform has had any impact on health literacy, all athletes will be asked to complete the Literacy in Musculoskeletal Problems,^30^ and the Health Literacy Survey European Questionnaire^31^ 1 week before the implementation of the webpage, and 6 months and 1 year following the implementation of the webpage (figure 2).

Focus group interviews concerning the delivery of the webpage, implementation, accessibility, feasibility, the health topics, use of the webpage and possible improvements will be conducted with athletes, coaches and stakeholders 6 months after the implementation. Following this evaluation, adjustments may be applied. Individual qualitative interviews with athletes, coaches and stakeholders will be conducted 1 year after implementation about the effect of the web platform, user behaviour and potential for improvement. Furthermore, it will be evaluated whether the uptake and effectiveness of the intervention is similar in the two countries (Sweden and South Africa) with different socioeconomic contexts.

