## Abstract

Elite Para athletes report a high incidence of sports injuries, illnesses and other health issues. Despite this, there are few prevention programmes in Para sport, and many of the existing prevention programmes are not adapted to Para athletes. To improve the success of preventive measures, it has been suggested that sports safety work should facilitate health promotion, including athlete health education. Therefore, the overarching aim of this project is to evaluate an accessible health promotion web platform as part of a complex intervention that aims to improve knowledge of athlete health in Para sport. In this protocol, the development, future implementation and evaluation of the intervention are described. To inform the implementation and use of such interventions, it is recommended to involve end users in the development and implementation process. Therefore, a participatory design process, including athletes and the sports organisation, was used to develop an accessible health promotion web platform. To evaluate this complex intervention, a process evaluation combining quantitative evaluation assessing causal pathways with qualitative methods assessing multifaceted pathways will be used. The primary outcomes are injury/illness incidence, athlete health parameters, health literacy and user behaviour. A cohort of elite Para athletes (n=150) from Sweden and South Africa will be invited to participate. This project will be the first that aims to improve athlete health in Para sport through pragmatic and accessible health promotion. It is a boundary-crossing project that will be conducted in a real-world sport setting, including athletes with different socioeconomic backgrounds.

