The overarching aim of this project is to develop, implement and evaluate an accessible health promotion web platform in a complex intervention that aims to improve knowledge of athlete health in Para sport. The specific aims that are described in this study protocol are: (1) to develop an eHealth-based and accessible health promotion web platform for Para athletes and their coaches, (2) to identify contextual factors within the sports and organisation that can facilitate the fidelity, implementation and use of such an intervention, (3) to assess whether a health promotion platform can reduce sports injuries and illnesses in elite Para athletes, (4) to assess whether such a platform can improve overall health parameters, such as sleep, nutrition and mental health in elite Para athletes and (5) to assess whether such a platform improves health literacy and changes behaviour among elite Para athletes.

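### The before/after incidence comparison is not tied to the same athletes, so risk-related leaving over about 4.5 years could pass for a platform effect in either direction

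*Protocol article*

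**What the plan says.** The third specific aim, at the end of the Introduction, is an effect aim: "to assess whether a health promotion platform can reduce sports injuries and illnesses in elite Para athletes". Process evaluation sets the outcome for it: "The primary outcome is the incidence of injuries and illnesses". The timing is "Data will be collected and analysed 6 months before implementation, 6 months after implementation and at 1 year and 4 years following implementation".

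Two sentences give the analysis: "Data will be analysed by describing incidence rates and proportions" and "A time-to-event analyses will be conducted". The second states no contrast between periods.

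On who is studied, the Abstract says "A cohort of elite Para athletes (n=150) from Sweden and South Africa will be invited to participate". Process evaluation says that, six months before launch, "all (approximately 150) athletes from the SPKs and the Maties Sports Club, South Africa, will be invited to participate in a longitudinal athlete health surveillance", with weekly self-report. It adds: "Due to a total population design, there is no power calculation". The Discussion names the lack of randomisation as a limitation. It does not mention a change in who contributes data.

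**The concern.** Without a concurrent control, evidence for the third aim has to come from comparing incidence before launch with incidence afterwards. The first window opens six months before launch and the last assessment is four years after it, so the span is about 0.5 + 4 = 4.5 years. A described rate in each window is an average over the athletes who contribute to that window. If those who stop contributing differ in injury risk from those who continue, the average moves even when no individual athlete's risk has changed.

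The article's own text makes wide differences in risk plausible. The Discussion refers to varied impairments and classifications across 28 sports and to comorbidity, and the interview results describe injuries that heal slowly.

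Two later uses of the result are exposed. The Discussion makes a future randomised trial conditional on success. Process evaluation also plans to compare effectiveness between Sweden and South Africa, and different patterns of leaving could produce a false difference between the two countries.

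**Working it through.** The article states no event rate, attrition rate or power calculation, so there is no figure to reproduce. The check asks how far composition alone can move the rate ratio when the platform does nothing.

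**Input from the article:** N = 150.

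**Assumptions, none from the article:** two risk groups; high-risk share 30% or 50%; high-risk rate 2 or 3 times the low-risk rate; each athlete's own rate constant.

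**Formula.** Let h and l be the numbers of high- and low-risk athletes at baseline, r the ratio of their rates, and dh and dl the proportions leaving.

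- Baseline mean rate = (h·r + l)/150
- Later mean rate = [h(1−dh)·r + l(1−dl)] / [h(1−dh) + l(1−dl)]
- Rate ratio = later / baseline

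**Worked cases**

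- Share 50%, r = 3, leaving 60% v 20%: baseline (75×3 + 75)/150 = 2.00; later (30×3 + 60)/90 = 1.667; ratio 0.83.
- Share 30%, r = 2, leaving 40% v 20%: baseline (45×2 + 105)/150 = 1.30; later (27×2 + 84)/111 = 1.243; ratio 0.96.
- Share 30%, r = 3, leaving 20% v 40% (reverse): baseline (45×3 + 105)/150 = 1.60; later (36×3 + 63)/99 = 1.727; ratio 1.08.

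**All combinations of share and rate ratio, no replacement of leavers**

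| Leaving, high v low risk | Rate ratio with no platform effect |
|---|---|
| 20% v 20% | 1.00 |
| 30% v 20% | 0.97–0.98 |
| 40% v 20% | 0.93–0.96 |
| 60% v 20% | 0.83–0.91 |
| 20% v 40% | 1.05–1.08 |

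If leavers were replaced, the 60% v 20% case gives 0.90–0.94 with newcomers at the baseline risk mix and 0.70–0.86 with only low-risk newcomers.

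**Second model.** Let injury-proneness Z be gamma with mean 1 and variance θ, and P(stay | Z) = exp(−cZ). Retention is then (1 + θc)^(−1/θ), and the mean proneness of stayers is 1/(1 + θc) = retention^θ. At an assumed 60% retention:

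- All loss related to proneness: 0.6^0.25 = 0.88, 0.6^0.5 = 0.77, 0.6^1 = 0.60.
- Half of the log-retention loss related to proneness (√0.6 = 0.775): 0.94, 0.88, 0.77.

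The 0.60 is an extreme: it needs θ = 1 and every departure driven by proneness.

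**Does restricting to athletes seen before and after cure it?** If leaving depends only on stable proneness, yes: each stayer's own rate is unchanged and the ratio is 1.00. If leaving follows the injuries that actually occur at baseline, no. Take Y baseline events with mean 2 (assumed) and P(stay | Y) = s^Y. Among stayers with proneness Z, the baseline mean becomes 2Z·s while the later mean is 2Z, so the within-athlete ratio is 1/s.

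- θ = 0: retention exp(−2(1−s)) = 0.6 gives s = 0.745 and a ratio of 1.34.
- θ = 1: retention 1/(1 + 2(1−s)) = 0.6 gives s = 0.667 and a ratio of 1.50.

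Stayers were then selected for a lucky baseline, and the restricted contrast shows harm where there is none.

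**The case against.** The strongest reply is that the article never says the rates are computed in whoever happens to report. It uses cohort and longitudinal wording and describes a single invitation before launch. It mentions the total population only to explain the absence of a power calculation. It is also a condensed account, so model details and missing-data rules may stand in a fuller plan.

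Much of this holds. A reader might infer that membership will change, or that new athletes will be added. The article states neither, and both remain inferences about elite squads over several years. A reader might also infer that the bias must flatter the platform. That is not supported either: injured athletes may leave more, but healthy athletes may equally tire of weekly reporting, and the reverse case gives an apparent harm. Nor is description the whole plan, since a time-to-event analysis is announced. With no contrast stated for it, however, it does not by itself deal with leaving that depends on risk.

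What survives is narrower. The article itself fixes a descriptive comparison across windows, up to four years after launch, as the means of answering an effect aim without a control. The cohort wording does not remove the problem, because a closed cohort is still exposed to selective loss. The point therefore rests on the stated method, not on missing detail.

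**Conclusion.** The point holds in this limited form: followed as written, the before/after comparison cannot separate a platform effect from a change in who contributes data. Whether a bias arises depends on leaving or non-reporting being related to risk; its direction depends on which athletes are lost.

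Under the stated assumptions and no platform effect, the rate ratio is about 0.83–0.96 when 40% to 60% of high-risk athletes leave against 20% of low-risk athletes. It is closer to 1 with a smaller difference, 1.00 with equal departure, and 1.05–1.08 with the reverse. These figures illustrate size only; the article supplies neither retention nor the spread of risk. The span over which athletes can be lost is longest for the 4-year comparison.

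**What to change.** For the incidence outcome, make the main before/after contrast an athlete-level model of the weekly reports: Poisson or negative binomial, with an athlete random effect and reported weeks as exposure. Use all reports from all athletes enrolled before launch, including those who later leave, so that leavers' baseline data count. In addition:

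- State whether the cohort is open or closed, and show any later entrants separately.
- Compare the baseline incidence of leavers and stayers.
- Give the contrast restricted to athletes reporting both before and after as a sensitivity analysis, noting that it can be biased upward if athletes leave because of baseline injuries.
- Treat the 6-month and 1-year contrasts as the main effect evidence and the 4-year figure as descriptive maintenance, because ageing and secular change remain even within athletes.

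The random-effect model is not a complete cure. It handles leaving that is explained by the reports already given; if leaving depends on proneness that those reports do not reveal, some bias remains. That is a reason to show the restricted contrast beside it.

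The cost is a little more analysis work and wider intervals at four years. No new data are needed, provided that weekly reports carry an athlete identifier, as longitudinal surveillance implies.

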## Discussion

This project will be the first that aims to improve athlete health in Para sport through pragmatic and accessible eHealth-based health promotion. It is a boundary-crossing project that will be in a real-world sport setting, including international researchers and sport organisations, and athletes training in different sport environments with different individual, geographical, social and economic ecosystems.

A limitation of the intervention could be the non-randomized control trial (RCT) design, as RCT design often is seen as the gold standard for evaluating an intervention.^19 32^ However, a crucial aspect in an RCT design is that the randomisation of the control group and intervention group is homogeneous and preferably matched, which is challenging in the Para sport population with a limited number of athletes, and athletes with various impairments and classifications participating in 28 different sports. Another crucial aspect is that RCT studies are most feasible when evaluating the effect of a single fixed intervention, for example, a specified dose of a drug.^32^ In contrast, injury and illness prevention in sport is complex, compromising multiple interacting components such as training background, general health, health literacy and coach and medical support as well as various outcomes such as acute injuries, overuse injuries, pain, general illnesses, overtraining and mental illness.^19^ Moreover, it has been shown that factors such as athlete behaviour and coaches’ perceptions of prevention may influence the outcomes of injury prevention,^5 8 12^ which are all factors that cannot be controlled within an RCT. In the Para sport population, interaction factors such as comorbidity from the impairment and various prerequisites may also interact with an intervention.

As many prevention studies in sport and exercise medicine fail to be implemented in a real-world sports context, it has been recommended to include the organisation, coaches and the target population itself in the development, implementation and evaluation,^6 17^ which also is supported by the Medical Research Council Guidelines, that suggest that a wider range and combination of research method advantageously could be used to improve interventions in real-world contexts.^18^ A strength of the current project is, therefore, that the implementation and evaluation of the implementation has been planned before the project starts. Also, the complex intervention design helps researchers and organisations to evaluate an intervention’s effectiveness, transferability and scalability in real-world contexts.^18 19^ A limitation is, however, that no participants from low-income countries have been involved in the development and implementation process. If this intervention is successful, it could, therefore, be suggested that a future RCT study can be conducted focusing on enrolling large multicentres of Para athletes from both low-income, middle-income and high-income countries, which also would allow us to randomise and match athletes.

## Data Availability

Data are available upon reasonable request. No data are available. This is a study protocol and hence no original data are available.
